#### Inclusion criteria

The study includes the following inclusion criteria:

Participants who aged between 18 and 70 years;Participants who meet the diagnostic criteria for Bell’s palsy, HBGS should be graded from II to VI, and the total score of SFGS should be ≤89;The onset is less than or equal to 3 days;The onset is unilateral; andParticipants who agreed to participate in the investigation and sign the written informed consent.

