### Sample size

The calculation of the sample size is based on the effective rate of acupuncture in the treatment of patients with Bell’s palsy in the acute stage. According to the previous studies (22, 23) and pre-experimental analysis of the research group, it is estimated that the effective rate of the EA group is 98%, the A group is 95%, the AC group is 85%, the SA group is 74%, and the BC group is 70%. We used PASS 15 software to calculate and set α = 0.05 and β = 0.1, and the results showed that the total sample size was at least 147 cases. It was observed that based on the ratio of the sample size of 1:1:1:1:1 in each group and considering the loss of follow-up rate of 10%, an optimal sample size of 33 participants should be recruited in each group. Therefore, a total of 165 participants should be recruited for this RCT.

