### Randomization

A random sequence will be generated based on block randomization by an independent research assistant using the software SPSS 26.0. The various eligible participants will be randomly divided into five groups with a 1:1:1:1:1 ratio. The treatment allocation codes will be enclosed by an independent researcher in sequentially numbered opaque envelopes until the first treatment schedule. To minimize coding interruptions, the chief investigator and result evaluators will also turn a blind eye to the treatment allocation.

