### Outcome measures

The outcome evaluation will be conducted at 6 time points, including the baseline, days 5, 10, and 20, and weeks 8 and 12 of treatment. In addition, SFGS and HBGS will be evaluated before each treatment to evaluate the recovery rate. Safety measures will be assessed at the baseline and day 20 of the treatment. The evaluation schedule is shown in Table 1.

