### Statistical analysis

The statistical analysis of this trial will use SPSS 26.0 software. To include the data of the participants who might withdraw later from the trial, all statistical analyses were based on the intention-to-treat population of all randomly assigned patients. Missing data will be analyzed using multiple imputations using the Markov chain Monte Carlo. The continuity data will be described as mean ± standard deviation (SD) or median and interquartile spacing. The classified data will be described with the frequency and percentage (*N*, %). The assessment of the difference between groups will use repeated measure analysis of covariance (ANCOVA) and trend chi-square, and the mixed effect model will also be used to evaluate the efficacy based on adjusting possible covariates. For results that require a comparison between multiple groups, Bonferroni will be used for multiple corrections. An interim analysis will be performed when half of the participants have completed the main outcome measurement.

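### The plan does not make a baseline-adjusted comparison primary for the binary day-20 effectiveness rate, which gives up some power although baseline SFGS and HBGS are collected

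*Protocol article*

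**What the plan says.** The protocol article (Primary outcome measures and Table 4) defines the primary outcome as the share of patients rated cured, efficacious or effective at the end of treatment on day 20. That corresponds to HBGS I–III and SFGS of 50 or more.

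On analysis, the Statistical analysis section states "The assessment of the difference between groups will use repeated measure analysis of covariance (ANCOVA) and trend chi-square", and the same sentence goes on to say that "the mixed effect model will also be used to evaluate the efficacy based on adjusting possible covariates". It does not say which of these methods tests the day-20 rate, and it names no covariate. Bonferroni correction is planned for multiple-group comparisons.

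On baseline data, the Outcome measures section says "The outcome evaluation will be conducted at 6 time points, including the baseline, days 5, 10, and 20", and Table 1 lists SFGS and HBGS at day 0. The Inclusion criteria require that "HBGS should be graded from II to VI, and the total score of SFGS should be ≤89". On allocation, the Randomization section says "A random sequence will be generated based on block randomization by an independent research assistant" and mentions no stratification by severity.

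**The concern.** The outcome is a cut of the same two scales that every patient has at baseline, and entry severity is wide. A patient who enters at HBGS II–III with SFGS 50–89 already satisfies Table 4 and counts as a success unless the palsy worsens. So far as such patients are enrolled, a link between baseline and outcome is built into the endpoint.

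Neither the allocation as described nor the only categorical test named uses that information. Repeated-measures ANCOVA is a method for continuous scores over several visits and does not fit a single-visit yes/no outcome. The mixed model comes in as an addition, with an open covariate list.

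What is at stake is precision at a fixed total of 165. The pairwise contrasts are the ones that answer the clinical questions, and they are weak after Bonferroni correction, so unused baseline information matters most there.

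**Working it through.** **Inputs from the protocol (Sample size section).** The planning rates are "the effective rate of the EA group is 98%, the A group is 95%, the AC group is 85" percent, and "the SA group is 74%, and the BC group is 70" percent. The error rates are "set α = 0.05 and β = 0.1". Five equal arms, 147 evaluable, 10% loss, 33 per arm, 165 in all.

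**Step 1: the plan's own figure.** The mean rate is (0.98 + 0.95 + 0.85 + 0.74 + 0.70)/5 = 0.844.
- Five-arm, 4-df likelihood-ratio test at 0.05 with 90% power: N = 148, against 147 stated.
- 147/0.9 = 163.3, rounded up to 164, hence 33 per arm and 165 in total, as stated.
- A Pearson effect size (w = 0.305) would need 166. A trend test with the arms ordered by rate would need about 112.

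The PASS procedure is not named, so the match is after the fact. The sizing looks like an unadjusted five-arm comparison.

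**Step 2: unadjusted pairwise power, 33 per arm.** Five arms give 10 pairs, so the Bonferroni level is 0.05/10 = 0.005.

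| Contrast | at 0.05 | at 0.005 |
|---|---|---|
| A vs SA | 0.66 | 0.32 |
| EA vs SA | 0.82 | 0.50 |
| A vs BC | 0.78 | 0.44 |
| AC vs BC | 0.31 | 0.09 |

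**Step 3: gain from adjustment.** The documents give no baseline-outcome correlation, so it is assumed and varied. The simulation has normally distributed latent severity, the planned rates, 30 evaluable per arm, and a linear model with and without a five-level baseline covariate (20,000 replicates).

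| Assumed latent correlation | A vs BC at 0.005 | Five-arm test at 0.05 |
|---|---|---|
| 0.3 | 0.402 to 0.421 | 0.907 to 0.917 |
| 0.5 | 0.396 to 0.450 | 0.908 to 0.934 |
| 0.6 | 0.401 to 0.479 | 0.906 to 0.940 |
| 0.7 | 0.407 to 0.515 | 0.904 to 0.949 |

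Null rejection was 0.046–0.056 at 0.05 and 0.003–0.005 at 0.005. A separate simulation at 33 per arm, using a linear risk-difference model with robust errors, gave about +1, +4 and +12 points for A vs BC at 0.005 under latent correlations 0.3, 0.5 and 0.7. It gave a loss of 1–2 points when baseline is unrelated to outcome, and type I error was again nominal.

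**Step 4: a range tied to Table 4.** Assume a share f enters at HBGS II–III, that 97% of them succeed in BC and SA, and that this binary status is the only covariate (33 per arm, 6,000 trials). A vs BC at 0.005 then goes from 47% to 49% (f = 0.2), 48% to 51% (0.3), 48% to 54% (0.4) and 47% to 56% (0.5). The protocol does not give f.

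**Step 5: sparseness.** Expected failures at 33 per arm are:
- EA: 33 × 0.02 = 0.66
- A: 33 × 0.05 = 1.65
- AC: 33 × 0.15 = 4.95
- SA: 33 × 0.26 = 8.58
- BC: 33 × 0.30 = 9.90

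The total is about 26 of 165. In a further simulation with a logistic outcome model at 33 per arm, ordinary adjusted logistic likelihood-ratio tests rejected a true null in 0.06–0.07 of pairwise comparisons at 0.05. The choice of adjusted method therefore matters.

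**The case against.** **The protocol never assigns the chi-square to the primary outcome.** A reader might infer that the day-20 rate is compared only by an unadjusted chi-square. The text does not support that. The sentence continues to an adjusted model for efficacy, a mixed model can be logistic, and a trend test needs ordered categories, so it may be meant for the four grades in Table 4. This stands. The point is only that no baseline-adjusted comparison is made primary, and that adjustment is additional with open covariates.

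**Details may sit in an analysis plan.** A covariate list can properly be left there, as can strata that a condensed article omits. Their absence is not the point. The point is the analysis that the article does state: a covariate-free categorical test, with adjustment as an extra.

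**The unadjusted test is valid.** This stands. A reader might infer that chance severity imbalance biases the comparison or swamps the planned differences. One SD of imbalance between two arms of 33 is √(2/33) = 0.246 SD. At latent correlation 0.5 the shift in a rate is the normal density at its cut × 0.5 × 0.246: about 4.0 points at 74%, but 1.3 at 95% and 0.6 at 98%. The shift is therefore well below the 3-point gap planned for EA vs A. For SA vs BC the planned gap is 4 points, but the sampling standard error is already √((0.74×0.26 + 0.70×0.30)/33) ≈ 11 points, and chance imbalance is part of that error.

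**Larger gains can be computed.** A variance factor of 1 − ρ² with ρ = 0.5 on the outcome scale would take 30 per arm to 30/0.75 = 40, and A vs BC at 0.005 from 39% to 56%. That is not a supportable figure. With a normally distributed baseline, the highest possible correlation with a binary outcome is density/√(p(1−p)): 0.103/0.218 = 0.47 at 95% and 0.048/0.140 = 0.35 at 98%. A value of 0.5 cannot occur within A or EA.

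**Adjustment has a cost with so few failures.** This stands in part and shapes the fix.

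**Conclusion.** The point holds as a matter of efficiency, not validity. The stated analysis does not make a baseline-adjusted comparison primary for an outcome whose baseline version is measured on everyone and is prognostic through the definition of success. Adjustment would change A vs BC power at 0.005 by about +1–2, +4–5 and +11–12 points at assumed latent correlations of 0.3, 0.5 and 0.7. The five-arm test would gain about 1 to 5 points, and type I error stays nominal with a suitable method. If baseline proved non-prognostic, the loss would be 1–2 points. These sizes rest on the planned rates and on assumed correlations and case mix. With pairwise Bonferroni power of 0.32 to 0.50 for the A and EA contrasts in Step 2, a moderate gain from data already in hand is worth taking.

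**What to change.** State in the Statistical analysis section that:
- The primary comparison of the day-20 effectiveness rate is an adjusted risk difference from a model with treatment arm and baseline SFGS as a continuous covariate.
- Because failures are sparse in EA and A, the model is either a linear risk-difference model with robust errors or Firth logistic regression with standardisation. One of the two is chosen in advance.
- The planned Bonferroni correction applies to these adjusted contrasts.
- Baseline SFGS replaces the open covariate wording for this analysis and is fixed before unblinding.
- The unadjusted chi-square is kept as a sensitivity analysis, and crude rates are reported by arm.

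The endpoint, visits and sample size stay as they are, and no new data are needed. The cost is a short text change, a model-based estimate that needs a sparse-data method and must be combined with the planned multiple imputation, and the 1–2 points of power lost if baseline turns out not to be prognostic.

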**Methods and analysis:**

In this randomized, controlled trial, 165 Bell’s palsy patients with unilateral onset within 3 days will be recruited and randomly assigned to either the electroacupuncture group (*n* = 33), the acupuncture group (*n* = 33), the sham acupuncture group (*n* = 33), the blank control group (*n* = 33), or the acupuncture control group (*n* = 33) in a 1:1:1:1:1 ratio. The participants will receive 4 weeks of treatment and 8 weeks of follow-up. The five groups of participants will receive the following treatments: A: Electroacupuncture + Medication (prednisone acetate tablets, mecobalamin tablets, and vitamin B1 tablets); B: Acupuncture + Medication; C: Sham Acupuncture + Medication; D: Medication only; and E: Acupuncture only. The primary outcome will be the effectiveness rate of different acupuncture modalities in improving facial nerve function after the intervention period. The secondary outcomes will be the recovery speed, the diameter of the facial nerve, the echo intensity and thickness of facial muscles, blood flow parameters of the facial artery, the serum inflammatory level, safety evaluation, and adverse events. Preliminary exploration of its mechanism of action occurs through inflammation and immune response. The difference between groups will be assessed using repeated measure analysis of covariance (ANCOVA) and trend chi-square.

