#### Primary outcome measures

The primary outcome is the effectiveness rate after the intervention period, which will be evaluated immediately at the end of treatment on the 20th day. Combined with the results of SFGS and HBGS, the efficacy evaluation criteria have been formulated according to the *Evaluation and efficacy standard of Integrated Chinese and Western Medicine for peripheral facial nerve palsy (draft)* by Yang et al. (25) as shown in Table 4. The effectiveness rate is calculated by dividing the sum of the number of cured, efficacious, and effective patients in each group by the number of patients in each group. The Sunnybrook facial grading system (SFGS) is composed of three distinct areas that generate a comprehensive score describing the overall static and dynamic state of the face. Final score = free movement points – static points – linkage points. SFGS score can range between 0 and 100, and the higher the score is, the better facial nerve function (26). The House-Brackmann facial nerve grading system (HBGS) is a scale for assessing the severity of Bell’s palsy, which can potentially classify facial nerve injury into six grades (27). Grade I indicates normal function, grade II mild dysfunction, grade ≤ IV moderate palsy, and grade ≥ V severe palsy (27). SFGS and HBGS scores will be evaluated prior to each treatment until the end of the study and during the follow-up periods of 8 and 12 weeks of treatment.

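### A trend chi-square is named for differences between five unordered arms; by elimination it appears to cover the binary day-20 primary outcome, where its result depends on how the arms are numbered

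*Protocol article*

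**What the plan says.** The Statistical analysis section names the methods for comparing groups: "The assessment of the difference between groups will use repeated measure analysis of covariance (ANCOVA) and trend chi-square". It adds that "the mixed effect model will also be used to evaluate the efficacy based on adjusting possible covariates", and it plans Bonferroni correction where several groups are compared. The abstract repeats the main statement: "The difference between groups will be assessed using repeated measure analysis of covariance (ANCOVA) and trend chi-square".

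On the primary outcome, the article says: "The primary outcome is the effectiveness rate after the intervention period, which will be evaluated immediately at the end of treatment on the 20th day". The rate is obtained by "dividing the sum of the number of cured, efficacious, and effective patients in each group by the number of patients in each group". The four grades of Table 4 are thus reduced to effective or ineffective for each patient.

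The abstract letters the arms A to E. A is electroacupuncture plus medication and B is acupuncture plus medication; the rest are "C: Sham Acupuncture + Medication; D: Medication only; and E: Acupuncture only". The Sample size section lists them in another order with the assumed rates, in per cent: "the effective rate of the EA group is 98%, the A group is 95%, the AC group is 85%, the SA group is 74". Medication alone comes last in that list, with an assumed rate of 70%. The article gives no numeric scores for the arms.

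**The concern.** A trend chi-square over groups (Cochran–Armitage, or linear-by-linear) gives each group a number and tests one slope across those numbers. That makes sense for doses or severity grades. Electroacupuncture plus medication, acupuncture plus medication, sham plus medication, medication alone and acupuncture alone are not steps on one scale. The test then answers a question that depends on the labels: it is sensitive to differences that line up with the numbering and insensitive to those that do not.

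Repeated-measures ANCOVA is a method for continuous outcomes. Among the between-group tests named, that leaves the trend chi-square for a binary rate at one time point. If it is used in that way, power can fall short of the design target. A significant result would also describe a trend with no clinical meaning.

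**Working it through.** **Inputs.** Assumed rates from the Sample size section: EA 0.98, A 0.95, AC 0.85, SA 0.74, BC 0.70, with α = 0.05, β = 0.1 and 1:1:1:1:1 allocation. The stated minimum is 147 in total, and 165 (33 per arm) after 10% loss. Two arm sizes are used below: 30 (147/5 = 29.4, rounded up) and 33 (all randomised).

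**1. The plan's own figure.** The mean rate is (0.98 + 0.95 + 0.85 + 0.74 + 0.70)/5 = 0.844. A 4-df test at α = 0.05 with 90% power needs a noncentrality of 15.405. The likelihood-ratio effect size is the mean over arms of 2[p ln(p/0.844) + (1 − p) ln((1 − p)/0.156)]:

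| Arm | Term |
|---|---|
| EA | 0.2107 |
| A | 0.1110 |
| AC | 0.0003 |
| SA | 0.0710 |
| BC | 0.1305 |

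The mean is 0.1047, and N = 15.405/0.10468 = 147.2, which matches the stated 147. Other routes give:

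- 4-df with unpooled variance: 150.0
- 4-df Pearson noncentral approximation: 165.4
- 1-df trend test, Sample size order: 111.0
- 1-df trend test, A–E order: 225.8

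The stated size therefore agrees with an order-free 4-df calculation and with neither trend calculation.

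**2. One data set, two orders.** Expected effective counts at 33 per arm, rounded: EA 32, A 31, SA 24, BC 23, AC 28. The total is 138/165 = 0.8364. With scores −2 to 2, T = Σ score × count, V = 33 × 0.8364 × 0.1636 × 10 = 45.16, and X² = T²/V on 1 df.

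- A–E order (EA, A, SA, BC, AC): T = −64 − 31 + 0 + 23 + 56 = −16; X² = 256/45.16 = 5.67; p = 0.017.
- Sample size order (EA, A, AC, SA, BC): T = −64 − 31 + 0 + 24 + 46 = −25; X² = 625/45.16 = 13.84; p = 0.0002.
- Pearson, 4 df: deviations from 27.6 are 4.4, 3.4, −3.6, −4.6 and 0.4, with squares summing to 65.2; X² = 65.2/4.516 = 14.44; p = 0.006 under any numbering.

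**3. Power by simulation at the planned rates** (100,000 or more trials per arm size).

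| Test | 30 per arm | 33 per arm |
|---|---|---|
| Trend, A–E order | 74% | 80% (79.4–79.5%) |
| Trend, Sample size order | 98% | 99% |
| Pearson, 4 df, any order | 91% | 94% |

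The large-sample approximation is lower for Pearson (87% at N = 150, 90% at N = 165) and for the A–E trend test (72% and 77%). The ranking does not change.

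**4. Empty cell.** The chance that EA has no non-responder is 0.98^30 = 55% or 0.98^33 = 51%. When that happens, an ordinary logistic model has no finite estimate for EA contrasts.

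**The case against.** **The article does not assign the trend test to the primary outcome.** This is true. It lists methods for all outcomes together, and the link rests on elimination. An unseen analysis plan may assign the tests or fix the scores. What stands is that the article names this test twice for differences between groups and offers no other categorical one.

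**The mixed model could serve.** A reader might infer that no named method can handle the primary outcome. That goes too far. The mixed model is named for efficacy, and with a binary link and arm as a nominal factor it would not depend on numbering. Nor does an empty EA cell defeat it: a 4-df likelihood-ratio test of arm still works, and only the EA estimates and Wald contrasts fail. The article does, however, present that model as an addition, for covariate adjustment.

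**Trend may refer to the ordered Table 4 grades.** In two-arm comparisons that would be sound and free of numbering. Across all five arms, a linear-by-linear test would still need arm scores, and the primary outcome collapses the grades anyway.

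**The harm is bounded.** Over all 120 numberings, trend power at 33 per arm runs from about 0.5% to 99%, and 76 numberings give p > 0.05 on the expected table. It would be wrong to take the lower end as a realistic risk, because it comes from an order (A, AC, BC, SA, EA) that the article never uses. With a code fixed in advance, type I error stays near 5%. That the code would be picked after seeing the data is only a possibility; the article does not say so.

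**Conclusion.** The point holds as a stated method that does not fit the design. Between the two orders that the article itself uses, trend-test power at the planned rates is 74% or 98% with 30 per arm, and 80% or 99% with 33. In the lettered A–E order it is about 10 to 16 percentage points below the planned 90%. The 4-df Pearson test reaches about 91% and 94% whatever the numbering, so the planned 165 is enough for it.

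This rests on three assumptions: that the trend test is meant for the day-20 rate, that it runs over all five arms with equally spaced scores, and that the Sample size rates are right. The agreement with 147 supports an order-free basis for the sample size but does not prove which procedure was run, since the article does not name it.

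**What to change.** For the day-20 effectiveness rate, replace the trend chi-square with a 4-df Pearson (or exact) chi-square across the five arms. Follow it with Bonferroni-adjusted pairwise comparisons in which arm is a nominal factor, and state that contrasts with an empty cell will use exact or penalised methods. Keep any trend or ordinal test for two-arm comparisons of the ordered Table 4 grades, and keep ANCOVA or the mixed model for the continuous outcomes.

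No extra patients, visits or data are needed. The cost is a wording change plus the ethics committee and registry approval that the article requires for any modification. It should be made before the group comparisons are run, including the planned interim analysis if that is still to come.

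### Single-step Bonferroni is valid, but Holm's step-down procedure would control the same familywise error and give more power per contrast at almost no cost

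*Protocol article*

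**What the plan says.** The Statistical analysis section fixes the multiplicity method in one sentence: "For results that require a comparison between multiple groups, Bonferroni will be used for multiple corrections". It does not list the contrasts or their number, and it mentions no step-down procedure. The same section analyses all randomised patients, imputes missing data, and plans an interim analysis when half of the participants have completed the main outcome.

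The Sample size section assumes effective rates of 98% (electroacupuncture plus medication, EA), 95% (acupuncture plus medication, A), 85% (acupuncture only, AC), 74% (sham plus medication, SA) and 70% (medication only, BC). For a type I error of 0.05 and power of 90%, it reports that "the results showed that the total sample size was at least 147 cases". After allowance for 10% loss, "an optimal sample size of 33 participants should be recruited in each group".

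**The concern.** With five arms, several pairwise contrasts matter. The Discussion says that the sham arm is there to separate real acupuncture from a placebo effect, so EA and A against SA and against BC carry the efficacy question. Single-step Bonferroni holds each contrast to 0.05/m for a family of m, however many others have already been rejected. Holm relaxes the threshold after each rejection and keeps the same error guarantee. At stake is some power on the key contrasts, in a single-centre trial with a three-day onset window whose authors expect that few patients may be available.

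**Working it through.** **Inputs.** From the Sample size section: rates 0.98, 0.95, 0.85, 0.74 and 0.70; α = 0.05; power 0.90; 33 per arm. The analysis of all randomised patients makes 33 the planned number per arm. About 30 per arm (33 × 0.9 = 29.7) shows the effect of 10% loss. Assumed here: two-sided pooled-z tests on complete binary data, and the families named below.

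**1. The plan's own figure.** The mean rate is 4.22/5 = 0.844. A five-arm any-difference test (4 df, α = 0.05, power 0.90) needs N = 148 with the likelihood-ratio noncentrality (w = 0.3235) and 150 with unpooled variance (w = 0.3205). Both are close to the stated 147. The Pearson form (w = 0.3052) needs 166 and a trend test 117. Loss: 147/0.9 = 163.3, so 164, which is 33 per arm and 165 in total. The stated size is therefore consistent with a global test and does not depend on the multiplicity method.

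**2. The two procedures.** Bonferroni rejects when p ≤ 0.05/m. Holm orders the p-values and compares the i-th smallest with 0.05/(m − i + 1), stopping at the first failure.
- m = 10: Bonferroni uses 0.005 throughout. Holm uses 0.05/10, 0.05/9, 0.05/8, and so on.
- m = 4: Bonferroni uses 0.0125 throughout. Holm uses 0.05/4, 0.05/3, 0.05/2, 0.05/1.

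No Holm threshold is below 0.05/m, so every Bonferroni rejection is also a Holm rejection. The first threshold is the same, so the chance of at least one rejection is the same.

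**3. All ten pairs.** Simulation of 100,000 trials, with z = |p₁ − p₂| / √(2p̄(1 − p̄)/n). Power in %:

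| Contrast | Bonferroni, n = 33 | Holm, n = 33 | Bonferroni, n = 30 | Holm, n = 30 |
|---|---|---|---|---|
| EA v BC | 64.5 | 70.3 | 62.5 | 64.1 |
| EA v SA | 47.5 | 56.7 | 47.6 | 49.7 |
| A v BC | 42.5 | 49.9 | 40.5 | 43.4 |
| A v SA | 27.6 | 35.8 | 26.9 | 30.1 |
| Mean | 45.5 | 53.2 | 44.4 | 46.8 |

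At least one rejection among the ten: 82.9% under both at n = 33, and 80.7% under both at n = 30. With all rates equal at 0.844 and n = 33, the simulated familywise error is 2.3% under both.

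**4. Only EA and A against SA and BC (four contrasts).** Mean power rises from about 67% to 77% at n = 33 and from about 62% to 71% at n = 30. The chance that all four are rejected rises from 33% to 55% at n = 33.

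**5. All four comparisons against BC, n = 33.** EA 84.5% to 84.8%; A 63.6% to 65.9%; AC 15.1% to 21.0%; SA 1.9% to 4.5%. At least one rejection: 88.6% under both.

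**6. Sensitivity.** For all ten pairs, part of the gain comes from the discreteness of the test. Mean Bonferroni power falls from 46.6% at n = 31 to 42.7% at n = 32. The Holm gain is 2 to 3 points at n = 28 to 31 and 7 to 8 points at n = 32 to 34. With Fisher tests at n = 33 the means are 39% and 43%. The four-contrast gain is stable for n = 28 to 35.

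**The case against.** Bonferroni is a standard, prespecified method that controls the familywise error. Nothing in the sentence is false or contradicted elsewhere, and Bonferroni gives simultaneous confidence intervals that agree with its tests. All of this stands. A reader might infer that power is given up for nothing, or that the plan is in error; the documents support neither.

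The size of the gain rests on an assumed family. An article may leave the contrast list to a fuller plan, and for comparisons against medication only the gain for EA and A is nearly nil. The simulated tests are also simpler than the planned trend chi-square and covariate-adjusted mixed model with imputation. So the percentages are illustrative. That Holm rejects everything Bonferroni rejects does not depend on the family.

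A reader might also infer that the trial becomes more likely to find something at all. Under Holm it does not, because the first threshold is the same.

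One might go further, to Shaffer's step-down entered after a significant five-arm test. With all ten pairs at 33 per arm, that raises the mean for the four key contrasts to 57% and the chance of any pairwise rejection to about 90%. But it adds an any-difference gate that the Statistical analysis section does not contain. In simulation it also lost a Bonferroni rejection in about 0.2% of trials at 33 per arm and about 1% at 30. It is optional and does not share Holm's strict dominance.

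**Conclusion.** The point holds as a low-cost efficiency improvement. For any family, Holm is at least as powerful as Bonferroni on every contrast at the same familywise error. At the plan's assumed rates and 33 per arm, the mean gain on the four key contrasts is about 8 points with all ten pairs (53.2 − 45.5 = 7.7; 46.8 − 44.4 = 2.4 at 30 per arm). It is about 10 points if only those four are tested. For EA and A it is 0.3 and 2.3 points if everything is compared with medication only.

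The change should not be read as a cure for low pairwise power. Under Holm the best contrast, EA v BC, reaches 70% with all ten pairs and 85% with comparisons against BC only, below the 90% used for sizing. At α = 0.005 the normal approximation asks for 55 per arm for EA v BC and 68 for EA v SA. That shortfall comes from a sample size that matches a global test, and it is a separate matter.

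**What to change.** In the Statistical analysis section, replace Bonferroni with Holm's step-down procedure, for example: 'Where several groups are compared, p-values will be adjusted by Holm's step-down procedure at a familywise level of 0.05.' Naming the family of contrasts in the same place would fix the size of the gain.

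Make the change before any interim comparison is seen. If interim results are already known, date the change and disclose it.

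The cost is one amended sentence and a routine p-value adjustment. Simultaneous intervals that match Holm's tests are less simple, but Bonferroni intervals can be reported beside the Holm-adjusted p-values. No extra patients are needed, and the omnibus-gated Shaffer procedure is not required.
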